### Adverse event management

An adverse event is defined as any untoward medical occurrence in a subject and does not necessarily have a causal relationship with this study. Potential adverse events would include any side effect or complication post invasive assessment including serological testing and muscle biopsies. Patients will be consented for each individual procedure performed.

Adverse events will be graded according to the Common Terminology Criteria for Adverse Events (CTCAE), the Principal Investigator will be informed immediately, and the appropriate action will be taken, with the event recorded in the CRF.

A serious adverse event (SAE) is an adverse event that fulfils one or more of the following criteria: results in death, is immediately life-threatening, requires prolongation of existing hospitalisation, results in persistent or significant disability or incapacity, or is an important medical condition. The causality of a serious adverse event will be assessed by the investigators and recorded on the SAE form. All SAEs will be notified to the sponsor’s Research and Development department via the SAE form in the case report form (CRF). Only those events classified as probable or related will be reported to the Research Ethics committee.

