### Muscle biopsy

This is the first study to attempt large samples of sequential muscle biopsies in these cohorts. It will allow the collection of safety data, however importantly, it allows comparison and analysis of functional and mass measures with muscle histology.

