### Safety

Whilst the main stay of this study is observational, there have only been a few studies which have performed muscle biopsies of the vastus lateralis in patients with significant comorbidities such as liver cirrhosis [79]. We will use a Bergstrom needle which is safe, uses a small incision and therefore has a reduced risk of infection and bleeding. Also, using the vastus lateralis is safer as there are limited motor units, with no major blood vessels or nerves traversing the biopsy site [80]. We will perform an ultrasound of the thigh prior to biopsy as part of the study; however, we will use this to additionally check for the optimum site, the presence of any aberrant vessels, and the depth from skin to muscle, to aid the biopsy procedure. A stringent safety checklist is in place to ensure that every patient is adequately risk assessed including allergies, equipment and personnel present. This includes a pre-biopsy check of their INR and clotting. A cut off of INR ≤ 1.6 and platelet count ≥30 will be used in concordance with national and local radiology guidance for procedures entailing a similar risk profile [81, 82]. All medications will be checked and any antiplatelet or anticoagulation medications will be noted. A biopsy procedure will not be undertaken in those for whom stopping medication may incur significant risk, e.g. warfarin for atrial fibrillation and increased stroke risk. If feasible, medication will be stopped for a minimum of 3 days in advance, in accord with drug half-life and national guidelines for endoscopic procedures [83].

All patients will have a point of care blood sugar (BM) checked pre biopsy procedure as those with diabetes and liver disease are at risk of hypoglycaemia from fasting. Those on any medications that need to be paused or hypoglycaemic including insulin will be contacted in advance and advised accordingly on adjustment of insulin doses the day prior to and of the biopsy and visit [84].

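### The SAE definition covers prolonging a hospital stay but not starting one, so a new admission for a biopsy complication need not be classed as serious

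*Protocol article*

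**What the plan says.** The relevant rules are in the protocol article under Adverse event management.

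- **Adverse events.** "Potential adverse events would include any side effect or complication post invasive assessment including serological testing and muscle biopsies". Each adverse event is graded by CTCAE, notified at once to the Principal Investigator, acted on, and entered in the case report form (CRF).
- **Serious adverse events.** "A serious adverse event (SAE) is an adverse event that fulfils one or more of the following criteria". The list is death, immediate threat to life, and then "requires prolongation of existing hospitalisation, results in persistent or significant disability or incapacity, or is an important medical condition".
- **What follows for an SAE.** The investigators assess causality and record it on the SAE form. Every SAE goes to the sponsor's Research and Development department.
- **Ethics committee.** "Only those events classified as probable or related will be reported to the Research Ethics committee".

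Elsewhere, the article says of the sequential biopsies (Muscle biopsy) that "It will allow the collection of safety data". It gives the reason such data are wanted (Safety): "there have only been a few studies which have performed muscle biopsies of the vastus lateralis in patients with significant comorbidities such as liver cirrhosis". Table 2 lists the number of hospital admissions as a disease complication in the CLD, IBD and RA cohorts.

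**The concern.** The hospitalisation criterion is "requires prolongation of existing hospitalisation", which only someone already in hospital can meet. This study mostly sees people who are not in hospital: a transplant assessment outpatient clinic, a NAFLD clinic, a nurse-led biologic clinic and a biologics registry for patients, and poster recruitment of staff and students for controls. For them the natural serious outcome of a biopsy complication, such as bleeding or infection, is a first admission, and that is not on the list.

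At stake is the SAE route itself and any SAE count quoted for the biopsies. The article presents that procedure as little studied in patients with cirrhosis and as a source of safety data.

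**Working it through.** No formula is needed for the defect itself; it follows from applying the definition to cases.

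**Step 1. Three versions of one complication, tested against the list.**

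| Case | Explicit criterion met? |
|---|---|
| Participant already an inpatient at the visit (allowed under Study schedule and method); the complication delays discharge | Yes, prolongation |
| Participant attends from home; the complication is immediately life-threatening, disabling or fatal | Yes, one of the other criteria |
| Participant attends from home and is newly admitted; not life-threatening, no significant disability | None |

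Only the third case is affected. There the sole remaining route is the last item, "or is an important medical condition", which the article does not define. Classification then depends on individual judgement. The first and third rows also sit badly together: one extra day for an inpatient is serious by rule, while a week-long new admission is not.

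**Step 2. Is new admission added anywhere else?** No. Table 2 counts admissions as an outcome of disease, does not link them to biopsy or to SAE status, and has no column for healthy controls. The route to the ethics committee under Monitoring and quality assurance is for serious breaches, not adverse events.

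**Step 3. What does the third case keep, and what can it lose?**

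| Kept (all adverse events) | Can be lost (SAEs only) |
|---|---|
| CTCAE grade | SAE form |
| Notification of the Principal Investigator | Recorded causality assessment |
| Entry in the CRF | Notification of the sponsor |
| | Any ethics committee report |

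**Step 4. How many procedures are exposed?** Patients may have two biopsies (visits 2 and 4) and controls one. Study design describes a further 20 NAFLD patients beyond the 50 with CLD; the abstract calls them a subset.

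- NAFLD additional: (50 + 20 + 50 + 50) × 2 + 20 = 360.
- NAFLD within the 50: (50 + 50 + 50) × 2 + 20 = 320.

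Both are ceilings, since biopsy is optional for participation and subject to its own exclusions. The article gives no complication or admission rate, so the number of affected admissions cannot be computed.

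**Step 5. The ethics committee threshold.** Naming probable separately from related suggests a graded causality scale, but the categories are not listed. The text does not settle whether a lower grade of relatedness exists and is withheld.

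**The case against.** The strongest reply is that little is lost. Biopsy complications are named as adverse events, and each is graded, escalated to the Principal Investigator and recorded whatever its label. The safety data promised under Muscle biopsy are not said to rest on SAE counts. The last item on the list can also capture a bleed or infection that leads to admission. All of this stands, and it limits the point to saying that such an admission need not be an SAE, not that it cannot be one.

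A second reply is that this is a condensed article and the full protocol may have the missing words. That is possible. But the article states the definition as a complete list, so the list is wrong as printed rather than abbreviated.

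A reader might infer four stronger things, none of which the documents support:

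- **That harm would go unrecorded or unrecognised.** The adverse event route is intact.
- **That possibly related events never reach the ethics committee.** The article lists no causality categories and never uses that grade, nor does it say which grade a biopsy bleed would receive. All SAEs go to the sponsor whatever their causality.
- **That the definition breaches Good Clinical Practice.** The article cites that standard without reproducing its SAE definition, so the comparison would need an outside source. The internal gap is enough.
- **That a particular number of admissions would be missed.** Any such figure needs a complication rate that the article does not give.

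**Conclusion.** The point holds as a defect in a stated rule. As written, a new admission for a biopsy complication that is not life-threatening or disabling meets no explicit SAE criterion. It could bypass the SAE form, causality assessment, sponsor notification and any ethics committee report. An SAE count for biopsies could therefore be too low, although the adverse event record would still contain the event.

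The size is unknown: at most 320 to 360 procedures are exposed, and only the subset in the third case of the table is affected. The conclusion assumes that the printed list is the operative definition and that investigators do not routinely bring new admissions in through the last criterion. The wording of the ethics committee threshold supports only a request for clarification.

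**What to change.** 1. Check the full protocol and SAE form. Unless they already do so, change the criterion to: requires inpatient hospitalisation or prolongation of existing hospitalisation.
2. Because recruitment began in January 2019, re-screen admissions after each biopsy against the corrected wording. Admissions recorded for Table 2 serve the disease cohorts. For the controls use the adverse event CRFs, because Table 2 does not cover them.
3. List the causality categories behind the probable-or-related rule, so that it is clear whether any lower related grade is withheld from the ethics committee.

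The cost is one wording change, one added list and a look-back through data already being collected. The main downside is more SAE forms, mostly for disease-related admissions in the CLD cohort. Planned admissions, such as for transplantation, can be exempted from expedited reporting to contain that.

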### Data management

All data for an individual participant will be collected by the PI or their delegated nominees and recorded in the case report form (CRF). Participant identification in the CRF will be through their unique Participant Study Number allocated at the time of consenting for the study. Data will be collected from the time the patient is considered for entry into the study through to completion of the study. All clinical data will be stored as per NHS regulations and held on a protected database. We will require some data which may be patient identifiable from Hospital Episode Statistics; however, these data will then be inputted in a non-identifiable manner under the standardised data collection guidance to ensure confidentiality and security.

Data from the CRF will be entered onto a secure password protected RedCap database held on a password-protected area within a University Hospitals Birmingham (UHB) NHS Foundation Trust server. Some research data may also be transferred to the University of Birmingham anonymously for further research purposes. Patients will be consented for this. Due care will be taken to ensure data safety and integrity, and compliance with the Data Protection Act 2018. All essential documentation and trial records will be stored in conformance with the applicable regulatory requirements and access to stored information will be restricted to authorised personnel. Coded research data will be stored for 10 years anonymously under the property of UHB NHS Foundation Trust in keeping with good clinical practice.

### Case report forms

CRFs will include baseline/follow-up medical history and physical examinations, comorbidities and concomitant medications. Additional information incorporated in the electronic database will include basic clotting and full blood count, observations, anthropometric data, bioimpedance analysis, completion of ultrasound, MRI, and muscle biopsy (visit 2 and 4 only), recorded for each visit. Other CRFs will include AE reporting.

### Patient and public involvement (PPI)

We designed the study with ongoing participation of specific patient groups. We held an initial forum where we presented the study concept and design to a PPI group and received feedback which was incorporated into our design. All patient information sheets and documentation were reviewed by the Liver and Gastroenterology PPI group and a Rheumatology PPI group (at UHB) independently and modified accordingly. During the study, we have had ongoing input from the participants, some of which has been implemented during their experience.

A summary of the results will be disseminated to all participants at the end of the study following analyses.

### Monitoring and quality assurance

The study will be conducted according to the current guidelines for Good Clinical Practice (GCP). Any deviation, that does not result in harm to the trial subject or significantly affect the scientific value of the study, will be documented in the CRF and appropriate corrective or prescriptive actions taken.

Any serious breaches will be immediately reported to the Principal Investigator who will take whatever immediate action is required to safeguard the wellbeing of the participant. The Chief Investigator will notify the Sponsor immediately and the Ethics committee within 7 days of becoming aware of the serious breach.

### Dissemination and publication

Results will be presented at relevant national and international conferences and submitted for publication in peer-reviewed open access journals. Participants will be asked if they would like to be informed of the study results at the time of obtaining consent.

### Research governance

The study will be carried out in accordance with the Declaration of Helsinki, under Good Clinical Practice guidelines. This study is not a Clinical Study of an Investigational Medicinal Product, and thus is not governed by the Medicines for Human Use (Clinical Trials) Regulations 2004.

## Discussion

This is the first observational study to deep phenotype sarcopenia using a multi-modal assessment method of both mass, function and strength and quality of life measures.

### Justification of study cohorts

Chronic inflammation is believed to result in an environment which contributes to sarcopenia, though the exact mechanisms remain unclear and may vary between different diseases. We selected this spectrum of chronic inflammatory diseases as in their extreme, acute presentations, the degree of sarcopenia can be profound. We recognise that the standard of care does vary within these cohorts, with biologic treatment in the RA and IBD cohorts and prehabilitation in the CLD cohort). However these were chosen to represent the spectrum of chronic inflammation. This will allow us to observe the mechanisms and findings across this wide spectrum. The CLD cohort comprise of patients with decompensated liver disease, who are in the end stage of their chronic inflammatory insult. In addition, the NAFLD subset represents early stages in a chronic inflammatory process with some of these patients having potential reversible fibrosis and in comparison, to the patients with ESLD, these patients have compensated liver disease. The RA and IBD cohorts will reflect those with a significant degree of disease severity to require treatment with a biologic agent. Whilst we appreciate that we can compare only some of the elements between cohorts, it will highlight possible trajectories of sarcopenia with treatments which may be further investigated.

### Challenges in study design

We have tried to incorporate previously validated measures of sarcopenia to compare to newer evolving assessments. For example, the using of validated L3 lumbar muscle cross-sectional area [50, 66–68], HGS of non-dominant limb, SPBB as a measure of functional capacity [69], and comparing these to more novel techniques such as ultrasound analysis of quadriceps muscles [70–72], and functional variables such as isokinetic dynamometry and physical activity [73, 74]. Importantly, segmental sarcopenia can occur in patients, therefore adequate assessment of global function is imperative to determine their degree of sarcopenia, and subsequent treatment and mortality risk especially in those undergoing liver transplantation assessment [66, 68, 75].

We are also investigating factors that affect sarcopenia such as sleep efficiency and quality [76, 77] and hope to correlate this to mass and functional variables. These may be important factors that should be considered to ameliorate sarcopenia.

Covert hepatic encephalopathy is frequent in patients with end-stage liver disease and as a result can affect cognition and is of relevance to this study, namely the ability to consent [78]. Many patients are commenced on rifaximin to treat and manage this. We will tackle this by ensuring an adequate period for the patient to read the PIS, having a family member or friend present during visits, reconfirming consent at each visit and performing full capacity testing on initial review and at each required interval. We will exclude any patients who had severe HE which would impact their ability to consent and consistently and adequately follow instruction and most importantly for their own safety.

### Confounding medications

Most patients with inflammatory disease are treated with a variety of medications. For the purposes of this study, we have allowed those on oral steroids or DMARDs in all cohorts. Additionally, those within the CLD cohort may have their follow up visits post liver transplantation, for which they will be treated with immunosuppression. Given it is unsafe to pause any of these, and this is an observational study, we are recording these data. We recognise it may compound muscle loss.

### Muscle biopsy

This is the first study to attempt large samples of sequential muscle biopsies in these cohorts. It will allow the collection of safety data, however importantly, it allows comparison and analysis of functional and mass measures with muscle histology.

### Safety

Whilst the main stay of this study is observational, there have only been a few studies which have performed muscle biopsies of the vastus lateralis in patients with significant comorbidities such as liver cirrhosis [79]. We will use a Bergstrom needle which is safe, uses a small incision and therefore has a reduced risk of infection and bleeding. Also, using the vastus lateralis is safer as there are limited motor units, with no major blood vessels or nerves traversing the biopsy site [80]. We will perform an ultrasound of the thigh prior to biopsy as part of the study; however, we will use this to additionally check for the optimum site, the presence of any aberrant vessels, and the depth from skin to muscle, to aid the biopsy procedure. A stringent safety checklist is in place to ensure that every patient is adequately risk assessed including allergies, equipment and personnel present. This includes a pre-biopsy check of their INR and clotting. A cut off of INR ≤ 1.6 and platelet count ≥30 will be used in concordance with national and local radiology guidance for procedures entailing a similar risk profile [81, 82]. All medications will be checked and any antiplatelet or anticoagulation medications will be noted. A biopsy procedure will not be undertaken in those for whom stopping medication may incur significant risk, e.g. warfarin for atrial fibrillation and increased stroke risk. If feasible, medication will be stopped for a minimum of 3 days in advance, in accord with drug half-life and national guidelines for endoscopic procedures [83].

All patients will have a point of care blood sugar (BM) checked pre biopsy procedure as those with diabetes and liver disease are at risk of hypoglycaemia from fasting. Those on any medications that need to be paused or hypoglycaemic including insulin will be contacted in advance and advised accordingly on adjustment of insulin doses the day prior to and of the biopsy and visit [84].

### Future consideration

At the end of the study, each participant will be invited to attend a focus group to

feedback on their experience of the study. This study will provide baseline data for consideration of a follow-on study focusing on intervention to potentially reverse or reduce the progression of sarcopenia in this patient group.

## Conclusion

This is the first study to use a multi-modal assessment model to phenotype sarcopenia in a spectrum of patients with chronic inflammatory disease. By selecting these diverse cohorts we hope to identify the common mechanisms driving sarcopenia whilst appreciating the individual differences that may arise. This unique comparison may highlight differences that need to be considered when assessing and treating sarcopenia across the spectrum of chronic inflammatory disease. We appreciate that these cohorts do require a separate standard of care treatments which limit comparison between groups. The enrolment of participants to the study commenced in January 2019 and is due to complete in July 2021. The full analysis is expected by Q1 2022.

## Data Availability

Not applicable.

## Abbreviations

RA: Rheumatoid arthritis
IBD: Inflammatory bowel disease
CLD: Chronic liver disease
EWGSOP: European Working Group on Sarcopenia in Older People
RFH GA: Royal Free Hospital Global Assessment
MELD: Model for End Stage Liver Disease
UKELD: United Kingdom Model for End Stage Liver Disease
11βHSD1: 11–beta hydroxysteroid dehydrogenase 1
CD: Crohn’s disease
UC: Ulcerative colitis
HMB: β-Hydroxy-β-methylbutyrate
PUFA: Polyunsaturated fatty acids
ESLD: End-stage liver disease
LT: Liver transplantation
IA: Inflammatory arthritis
EULAR: European League Against Rheumatism
NAFLD: Non-alcoholic fatty liver disease
IL: Interleukin
DHEA: Dehydroepiandosterone
DHEA-S: Dehydroepiandosterone sulphate
PBMCs: Peripheral blood mononuclear cells
HGS: Hand grip strength
MAMC: Mid-arm muscle circumference
TSF: Triceps skinfold thickness
SPPB: Short Physical Performance Battery
MRI: Magnetic resonance imaging
ACSA: Cross-sectional area
DEXA: Dual-energy X-ray absorptiometry
CT: Computerised tomography
SF-36: Short form-36
CLDQ: Chronic liver disease questionnaire
FACIT-F: Functional assessment of chronic illness therapy – fatigue
IBD –DI: Inflammatory bowel disease - disability index
PIS: Patient information sheet
CTCAE: Common terminology criteria for adverse events
SAE: Serious adverse event
CRF: Case report form
UHB: University Hospitals Birmingham
